### Statistical methods

The participant will be included in the analysis, once be randomized, regardless of whether or not the assigned intervention is received, in order to follow the “intention-to-treat” design.

For primary outcome, a chi-squared test will be carried out to evaluate the difference in cure rate at the final assessment between groups. For secondary outcome, a chi-squared test will be used to compare rates of improved NCS outcome between groups; Student’s *t*-tests will be used to assess the validity by matching individual initial and final scores.

Statistical significance was set at *p* < 0.05. Data were analyzed with the SPSS statistical package [SPSS (Statistical Package for the Social Sciences) Inc., Chicago, IL, USA], version 19.

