### Sample size

The sample size for this study was calculated based on a standard two-sided trial with a continuous outcome, and the calculations assume 5% type I error with 80% power. According to an average 30% dropout rate in long-term follow-up period, we anticipate that we will require 280 total participants.

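### The only t-test stated for secondary scores matches initial to final values, and no between-arm comparison is stated for quality of life (IXTQ) or refraction

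*Protocol article*

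**What the plan says.** The section Proposed outcome measures lists three secondary outcomes: improvement on the NCS, quality of life on the IXTQ, and refractive change.

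The section Statistical methods covers all secondary analysis in one sentence with two clauses:

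- For the NCS, "a chi-squared test will be used to compare rates of improved NCS outcome between groups".
- Then come Student's t-tests, which "will be used to assess the validity by matching individual initial and final scores".

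The primary analysis, in the same section, is explicit about the contrast: "a chi-squared test will be carried out to evaluate the difference in cure rate at the final assessment between groups". The significance level is 0.05 throughout.

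The t-test clause differs from the other two. It does not mention groups, does not name an outcome, and gives its purpose as assessing validity, which is not a treatment comparison.

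**The concern.** The trial is randomised in order to compare surgery with observation. A test that matches each child's first score to that child's last score asks whether children changed, not whether the arms differ.

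Children enter between 5 and 18 years of age and are followed for 5 years. Refraction and quality of life can plausibly shift over that time in both arms whatever the treatment. Entry thresholds on deviation and stereoacuity also make some regression to the mean plausible in related measures. A paired p-value within an arm absorbs all of this together with any effect of surgery.

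The risk is in how the results would be read. If change is significant after surgery and not under observation, the pair of p-values invites a conclusion about treatment that neither test supports. An analysis that follows the sentence as written would leave two of the three secondary outcomes without an estimate of the difference between randomised arms.

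**Working it through.** **1. What is stated for each secondary outcome**

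| Outcome | Between-arm test stated | Other test stated |
|---|---|---|
| NCS | Yes, chi-squared on improvement rates | Possibly the matched t-test |
| IXTQ | None | Possibly the matched t-test |
| Refraction | None | Possibly the matched t-test, though refraction is not naturally called a score |

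If the t-test clause covers IXTQ and refraction, they have a test without an arm contrast. If it covers only the NCS, they have no stated test. Either way, no randomised comparison is stated for two of the three outcomes.

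**2. Numbers available for the illustration**

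From the Sample size section: "we anticipate that we will require 280 total participants", and "According to an average 30% dropout rate in long-term follow-up period". Allocation is 1:1. Assuming that dropout falls equally on the arms:

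280 × (1 − 0.30) = 196 evaluable; 196 / 2 = 98 per arm.

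The article says that the size was "calculated based on a standard two-sided trial with a continuous outcome" and that "the calculations assume 5% type I error with 80% power". It gives no effect size or SD, so 280 cannot be reproduced from its own inputs. Solving backwards for the detectable standardised difference:

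(1.960 + 0.842) × √(2/98) = 2.802 × 0.1429 = 0.40.

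Forwards, 0.40 needs 99 per arm, and 198 / 0.70 = 283, close to 280. The value 0.40 is inferred here and is not stated in the article. It shows that a two-sample comparison of change would have 80% power for a difference of 0.40 SD.

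**3. How paired tests behave when surgery has no effect**

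Assumptions: 98 per arm, normally distributed change scores with SD 1, the same mean drift in both arms, two-sided 5% tests. The drift is in SDs of the change score. No drift appears in the document, so a range is shown. Results are from 10,000 simulated trials at each drift.

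| Shared drift (SD) | Paired test significant in surgery arm | Exactly one arm significant | Two-sample test of change significant |
|---|---|---|---|
| 0 | 5.2% | 9.6% | 4.9% |
| 0.1 | 17.2% | 28.1% | 5.0% |
| 0.2 | 50.3% | 50.6% | 4.9% |
| 0.3 | 84.3% | 26.6% | 4.6% |
| 0.5 | 99.8% | 0.4% | 5.4% |

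Check: if each arm is significant with probability p, independently, exactly one is significant with probability 2p(1 − p).

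- At 0.1 SD: 2 × 0.172 × 0.828 = 0.285.
- At 0.2 SD: 2 × 0.503 × 0.497 = 0.500.
- At 0.3 SD: 2 × 0.843 × 0.157 = 0.265.

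These agree with the table within simulation error. The expression cannot exceed 0.50, so the row at 0.2 SD is the worst case.

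The second column carries a separate warning. At a drift of 0.3 SD or more, a reader who looks at the surgery arm alone sees a significant change in at least 84% of trials in which surgery does nothing.

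**The case against.** The strongest reply is that the sentence is ambiguous and the article is a condensed one. The t-test clause follows the NCS clause and speaks of scores, so it may concern only the NCS. Matching initial and final values is also how per-child changes are formed before a two-sample t-test. The article does not say that the test is done within groups. A fuller protocol or analysis plan, not shown, may contain the comparison. Initial-to-final testing also has a legitimate use here, because the secondary objectives include describing the natural course of the condition.

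Part of this stands. A reader might infer that IXTQ and refraction are never compared between arms. The document does not support that: it states no such comparison but does not exclude one. Nor does it say that significance in one arm alone will be taken as evidence for surgery.

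Three other inferences also go too far:

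- **That the NCS lacks a sound comparison.** The chi-squared test on improvement rates is a valid between-arm test and matches the outcome as defined. Reducing the score to improved or not improved costs power but is not an error.
- **That paired IXTQ scores mix different forms as children age.** The article calls the quality-of-life evaluation age-specific but describes no separate versions.
- **That the false-inference rate is 50%.** That is the ceiling of 2p(1 − p), reached near an assumed drift of 0.2 SD. It is about 10% with no drift and under 1% at 0.5 SD.

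The reply does not remove the core. The section specifies a contrast between groups for two tests and not for the third. The likeliest reading of that third test is paired, and a plan that carried it forward would carry the weakness too.

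**Conclusion.** The point holds in a limited form. A between-arm test is stated for one secondary outcome of three. The only other secondary analysis reads as a paired initial-to-final test on unnamed scores, and no randomised comparison is stated for IXTQ or change of refraction. A named test that cannot isolate the effect of surgery is more than a detail left for later.

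Under no arm difference, discordant paired results occur in about 0.4% to 51% of trials across assumed drifts of 0 to 0.5 SD, against about 5% rejection for a two-sample test of change. These figures rest on 98 evaluable per arm, equal dropout, normal change scores and drifts that are assumed and not taken from the document. They illustrate the mechanism and do not predict this trial's error rate.

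The consequence is confined to secondary outcomes. The primary outcome has its own between-arm test under intention to treat and is not affected. The sentence should be corrected before the final analysis.

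**What to change.** Rewrite the secondary-outcome sentence under Statistical methods, and carry the same wording into the analysis plan:

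1. Name the scores to which each test applies.
2. For IXTQ and for refraction, compare the arms at the final assessment by ANCOVA, with the final value as outcome and arm, baseline value and age as covariates. Report the adjusted between-arm difference with its 95% CI.
3. Keep paired initial-to-final changes only as a description of the course within each arm, labelled as such, with no treatment conclusion drawn from comparing their p-values.
4. Drop or explain the stated purpose of assessing validity.

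The chi-squared test for the NCS may stay.

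The cost is wording only. The Clinical tests section lists the IXTQ and cycloplegic refraction at each visit, so baseline and final values are already being collected.

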### Potential risks and adverse events

We conduct active monitoring in both groups for potential risks, especially for the observation group for a natural deterioration in their IXT condition. This risk will be managed biannually for the duration of follow-up period, and the treatment will be offered if needed. Adverse event and serious adverse event following strabismus surgery will be recorded and undertaken properly.

### Auditing plan

The ethics committee will meet and communicate important protocol modifications if necessary. Members of the trial steering committee will meet biannually to audit trial conduct.

### Protocol amendments

Any changes to the protocol will be reported to the ethics committee by the trial steering committee. Any modifications from the protocol will be fully documented using a breach report form. The modified protocol will also be synchronized in the clinical trial registry.

### Dissemination policy

The results of the study will be released to the public via publications.

## Trial status

Recruitment to the SOMIX trial commences in November 2015 and is ongoing at the time of this manuscript submission. Recruitment of the trial was originally scheduled to end in October 2017, but we have extended this phase up to October 2022 in consideration of low enrollment rate after initial screening. Planned follow-up assessments of both groups are orderly conducted.

## Protocol version

Protocol ID (ZX201304) of December 21, 2021.

## Data Availability

Any data required to support the protocol can be supplied on request.

## Abbreviations

IXT: Intermittent exotropia
RCT: Randomized controlled trial
BSV: Binocular single vision
BCVA: Best corrected visual acuity
PACT: Prism and alternative cover test
NCS: Newcastle control score
IXTQ: Intermittent exotropia questionnaire
PD: Prism diopters
D: Day
W: Week
M: Month
Y: Year
